| (e) | Details of procedure and methodology proposed to be used (300 words) including description of the potential risks and benefits, exclusion and Inclusion criteria outcome measures, statistical analysis:  ***Patient population:*** *Covid-19 positive symptomatic cases either non-severe or severe category*  ***Intervention:*** *Two therapeutic interventions for non-severe category and three for severe category as described below*  ***Comparator:*** *Parallel arm design, compared among other interventional arm in same category*  ***Outcomes:*** *Clinical and laboratory improvements in 72 hours of treatment*  **Patient population-**  Patients diagnosed with SARS-CoV-2 infection after positive reverse-transcriptase–polymerase chain reaction (RT-PCR) assay.  **Inclusion criteria:**   1. Age ≥18 years at time of participation in the study 2. Laboratory (RT-PCR) confirmed infection with SARS-CoV-2 3. Symptomatic (severe or non-severe) Covid-19 disease 4. Willingness of study participant to accept randomization to any assigned treatment arm   **Exclusion criteria:**   1. Use of medications that are contraindicated with Lopinavir/Ritonavir, Hydroxychloroquine/Chloroquine, or Ribavirin and that cannot be replaced or stopped 2. Patient already on antiretroviral therapy with Lopinavir-Ritonavir based regimen or on Hydroxychloroquine/Chloroquine or on Ribavirin 3. Any known contraindication to test drugs such as retinopathy and QT prolongation 4. Known allergic reaction or inability to delivery oraly to Lopinavir-ritonavir, Hydroxychloroquine/ Chloroquine, Ribavarin 5. Pregnant or breastfeeding females 6. Receipt of any experimental treatment for 2019-nCoV (off-label, compassionate use, or trial related) within 30 days prior to participation in the present study or want to participate after enrolment   **Potential benefits:**   1. All those who participate in the trial will benefit from possible effective treatment for COVID-19 infection 2. The study will highlight the therapeutic options in management of the symptomatic patients of COVID-19 infection   **Potential risks:**  The present study will be conducted on symptomatic patients of COVID-19 attending AIIMS Rishikesh. The patients will be categorised based on severity and treatment will be allocated accordingly.  Adverse drug reactions, though not frequent may be associated with the treatment. Proper supportive management will be given to the patients at the institute.  **Methodology**:  **Flow Diagram**  Patients of COVID-19 infection - After confirmation by RT-PCR at AIIMS, Rishikesh  Screening for inclusion in trial Enrolment Excluded  ♦  Not meeting inclusion criteria  ♦  Declined to participate  ♦  Other reasons  Categorisation based on severity of patient  **SEVERE group**  **NON-SEVERE group**  Randomisation to treatment arm:  **A. Standard Treatment (ST-S)**  **B. Hydroxychloroquine + Ribavirin + ST-S**  **C. Lopinavir+ Ritonavir + Ribavirin + ST-S**  Randomisation to treatment arm:   1. **Standard Treatment (ST-NS)** 2. **Hydroxychloroquine + Ribavirin + ST-NS**  RandomisationAllocation Monitor progress of patient in 72 hours Follow-Up Patient improve- continue same treatment  Clinical evaluation- @72 hours  Improve - Continue same treatment  Progress – achieved end point and Shift to institute protocol for further treatment  Patient do not improve/ Signs of severe disease  Shift to **SEVERE group** treatment arms after randomization with new consent Analysis Analysis  **Total duration of observation**:  28 days from the time of enrolment into the study OR till patient is discharged or death whichever is longer  **Design:** Open label, Parallel arm design, stratified randomised controlled trial:  Patients will be screened for the study after diagnosis of COVID-19 infection by Microbiology team. Patients will be categorised as non-severe or severe based on predefined criteria. The patient will be enrolled in the study after a written informed consent. Since it is an exploratory trial as COVID-19 being a new disease, all patients who came under the purview of the inclusion criteria within the study period and who have consented for the study will be included. Clinical evaluations will be done by a separate investigator. Blinding will not be performed but dynamic randomization will be done. Patients will be followed up for a period of 28 days from the day of enrolment.  At the time of enrolment, demographic information will be collected from participants, and relevant data on their medical histories, comorbidities, and risk factors for severe COVID-19. It will be documented along with investigations including CBC, ECG, LFT, RFT, G6PD status.  The patients will be categorised as severe based on the following criteria:   - Confirmed pneumonia on chest imaging, SPo2 <93%, Pao_2_:Fio_2_ <300 mg Hg - Respiratory failure (need of mechanical ventilation) - Septic shock - Multiple (>2) organ dysfunction syndrome (MODS) - Liver disease (Child Pugh score ≥ C, AST>5 times upper limit) - Patients with known renal impairment (estimated glomerular filtration rate ≤30 mL/min/1.73 m2) or receiving continuous renal replacement therapy, haemodialysis, peritoneal dialysis - Other single organ failure (e.g. heart, pancreas, etc) if specific definition meets   Non-severe category includes mild and moderate disease severity category other than severe ones.  **Treatment Schedule**  **Non-severe Treatment arms (NS-group):**   \| **Treatment Arm** \| **Drug** \| \| --- \| --- \| \| A \| Standard Treatment (ST_NS_) \| \| B \| Hydroxychloroquine 400 mg twice on first day followed by 400 mg per oral daily for 10 days + Ribavirin (2.4 g orally as a loading dose followed by 1.2 g orally every 12 hours) for 10 days + Standard Treatment (ST_NS_) ^6^ \|   **Standard Treatment for non-severe cases (ST_NS_):**   1. Strict Isolation 2. Standard Precautions (Hand hygiene, Cough Etiquette, Wear surgical mask) 3. Hydration 4. Proper Nutrition 5. Supportive Pharmacotherapy (Antipyretic, Antiallergic, Cough Suppressant) 6. Treatment of Comorbid Diseases 7. Oseltamivir (75 mg BD) for patient who are tested positive for H1N1   If the patient improves clinically the same treatment will be continued. If the patient do-not improve or shows sign of severity (mentioned above) the patient will be shifted to the severity arm (S-group) of the clinical trial and again randomization will be done and enrolled after new consent only for severe group. However, if intervention falls on HCQ arm, then it will be taken as end point reached and shifted to institute treatment protocol for further management.  **Severe group Treatment arms (S-group):**   \| **Treatment Arm** \| **Drug** \| \| --- \| --- \| \| A \| Standard Treatment (ST_s_) \| \| B \| Hydroxychloroquine 400mg BD on day1 followed by 400 mg once daily + Ribavirin (2.4 g orally as a loading dose followed by 1.2 g orally every 12 hours) for 10 days + Standard Treatment (ST_s_) \| \| C \| Lopinavir(400mg) + Ritonavir (100mg) two tablets twice daily+ Ribavirin (2.4 g orally as a loading dose followed by 1.2 g orally every 12 hours) for 10 days + Standard Treatment (ST_s_)^6^ \|   **Standard Treatment for severe patients: (ST_s_)**   1. Strict Isolation 2. Standard Precautions (Hand hygiene, Cough Etiquette, Wear surgical mask) 3. Fluid Therapy 4. Supportive Pharmacotherapy (Antipyretic, Antiallergic, Cough Suppressant) 5. Oxygen supplementation (As required) 6. Invasive ventilation (As required) 7. Antibiotic agents for other associated infections (according to 2019 ATS/IDSA guidelines for non-ICU and ICU patients) 8. Vasopressor support 9. Renal-replacement therapy 10. Treatment of Comorbid Diseases 11. Oseltamivir (75 mg BD) for patient who are tested positive for H1N1   Patients will be assessed for clinical and laboratory improvements in 72 hours of treatment. In case the patient does not respond to the current treatment regimen the patient will be shifted to institute protocol for current practice of treatment.  **Timelines of investigations: Repeated at 72hrs interval**   \| Investigations \| Baseline \| Next 72hrs \| \| --- \| --- \| --- \| \| CBC \| **✔** \|  \| \| LFT \| **✔** \|  \| \| KFT \| **✔** \|  \| \| HBA1C and Blood sugar \| **✔** \|  \| \| RT-PCR for SARS-Cov-2 (until 24hrs apart twice negative) \| **✔** \|  \| \| PT/INR \| **✔** \|  \| \| Serum Electrolytes \| **✔** \|  \| \| ABG \| **✔** \|  \| \| Chest Xray \| **✔** \|  \| \| ECG \| **✔** \|  \| \| Other organ markers as per involvement \| **✔** \|  \|     **Dose Modifications:**  If any serious adverse event is recorded, the participant will be withdrawn from the trial and management will be done accordingly as per institute policy.  **Recording adverse events:**  All adverse events will be recorded in the medical records in the first instance. All adverse events will be recorded with clinical symptoms and accompanied with a simple, brief description of the event, including dates as appropriate. Each adverse event will be assessed for severity, causality, seriousness and expectedness and informed to IEC within 24hours.  **Discontinuation/withdrawal of participants:**  A participant may be withdrawn from trial treatment whenever continued participation is no longer in the participant’s best interests, but the reasons for doing so must be recorded.  Reasons for discontinuing treatment may include:   1. Unacceptable drug toxicity 2. Development of progressive disease 3. Patients withdrawing consent to further trial treatment   **Endpoints:**  **Primary endpoints:**   1. Time to Clinical recovery (TTCR)    - TTCR is defined as the time (in hours) from initiation of study treatment (active or placebo) until normalisation of fever, respiratory rate, and oxygen saturation, and alleviation of cough, sustained for at least 72 hours.    - Normalisation and alleviation criteria: 2. Fever - ≤36.9°C or -axilla, ≤37.2 °C oral 3. Respiratory rate - ≤24/minute on room air 4. Oxygen saturation - >94% on room air 5. Cough- mild or absent on a patient reported scale of severe, moderate, mild, absent 6. Time to SARS-CoV-2 RT-PCR negative in upper respiratory tract specimen 7. Time to laboratory recovery of each organ involvement   **Secondary Endpoints:**   1. All causes mortality 2. Frequency of respiratory progression  - Defined as SPO2≤ 94% on room air or PaO2/FiO2 <300mmHg and requirement for supplemental oxygen or more advanced ventilator support.  1. Time to defervescence (in those with fever at enrolment) 2. Frequency of requirement for supplemental oxygen or non-invasive ventilation 3. Frequency of requirement for mechanical ventilation 4. Frequency of serious adverse events as per AIDS table grade of severity   **Statistical analysis**:  All COVID-19 positive patients will be included in the study after informed consent. Since it is an exploratory trial as COVID-19 being a new disease, all patients who came under the purview of the inclusion criteria within the study period and who have consented for the study will be included. Data will be described as mean+ SD for most of the parameters. Comparisons of the descriptive variables of the two arms will be performed using the Wilcoxon rank sum test for continuous variables and the chi-square or Fisher’s exact test for categorical variables. Primary analysis will include all patients (Intention to treat) and sub-group populations (per-protocol).  **Ethical clearance:**  The present study deals with a new infectious disease which has no definite treatment. Current therapy is based on symptomatic treatment. The present study explores the possibilities of new drugs in SARS-CoV-2 infection. The study will be conducted after IEC approval. Written informed consent will be taken from all participants.  **Safety Outcomes**  Safety outcomes will be determined according to the division of AIDS table for grading severity of adult adverse events (<https://rsc.niaid.nih.gov/clinical-research-sites/daids-adverse-event-grading-tables>), with specific focus on the events of gastrointestinal tract, arrhythmias, myopathies. In case of serious ADRs including death, compensation will be given as per institute protocol. |

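### The protocol withdraws patients from the trial after any serious adverse event, which contradicts its own 28-day follow-up, intention-to-treat analysis and treatment-only discontinuation wording

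*Protocol*

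**What the plan says.** All of this is in section (e) of the Protocol unless stated otherwise.

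- **Dose Modifications:** "If any serious adverse event is recorded, the participant will be withdrawn from the trial and management will be done accordingly". The rule is mandatory, has no causality condition, and refers to the trial, not the drug.
- **Discontinuation/withdrawal of participants:** "A participant may be withdrawn from trial treatment whenever continued participation is no longer in the" participant's best interests. This is discretionary and concerns treatment. Toxicity, progressive disease and withdrawn consent are listed as reasons for stopping treatment.
- **Design:** "Patients will be followed up for a period of 28 days from the day of enrolment". Total duration of observation gives "28 days from the time of enrolment into the study OR till patient is discharged or death whichever is longer".
- **Statistical analysis:** "Primary analysis will include all patients (Intention to treat) and sub-group populations (per-protocol").
- **Endpoints:** recovery, RT-PCR clearance and laboratory recovery are primary. All-cause mortality, respiratory progression, ventilation and SAE frequency are among the secondary endpoints. Clinical recovery runs "until normalisation of fever, respiratory rate, and oxygen saturation, and alleviation of cough, sustained for at least 72 hours".
- **Flow Diagram:** a patient who progresses has "achieved end point and Shift to institute protocol for further treatment".
- **Treatment Schedule:** for non-severe patients who do not improve and are randomised again, "if intervention falls on HCQ arm, then it will be taken as end point reached and shifted to institute treatment protocol for further management".

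**The concern.** Several endpoints, mortality and mechanical ventilation above all, can occur after a first SAE. A rule that takes the patient out of the trial at that SAE stops data collection just when these outcomes become likely. The severe stratum admits patients with respiratory failure, septic shock or multiple organ dysfunction, so SAEs caused by the disease itself are to be expected.

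This is more than a matter of analysis. A statistical analysis plan can say how withdrawn patients are handled, but it cannot recover outcomes that were never collected. The trial is also open label, so the recording of an SAE, and with it exit from the trial, can be influenced by knowledge of the arm.

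The unnamed end point is a smaller, separate matter. The first primary endpoint is recovery, and the phrase is attached to patients who are failing. Without a named event, different people may code it differently.

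**Working it through.** **Setting the passages side by side**

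| Question | Dose Modifications | Other text in section (e) |
|---|---|---|
| What is stopped after an SAE? | The trial | Trial treatment (discontinuation section) |
| Is it mandatory? | Yes | No, discretionary |
| How long is the patient observed? | Until the SAE | At least 28 days |
| Who is analysed? | Outcome data end at the SAE | All patients, intention to treat |

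The left column and the right column cannot both be followed for a patient with a non-fatal SAE before day 28.

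**Illustrating the size**

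The protocol gives no sample size, SAE rate or event rate, so there is no figure of its own to reproduce. Every rate below is an assumption.

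Inputs: SAE proportion *s* of 5% in one arm and 20% in the other; death 2% without an SAE and 30% after one.

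- True deaths = (1 − *s*) × 0.02 + *s* × 0.30
  - 5% arm: 0.95 × 0.02 + 0.05 × 0.30 = 0.019 + 0.015 = 3.4%
  - 20% arm: 0.80 × 0.02 + 0.20 × 0.30 = 0.016 + 0.060 = 7.6%
- Deaths seen if nothing after the SAE is recorded = (1 − *s*) × 0.02
  - 5% arm: 1.9%; 20% arm: 1.6%

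Other assumed SAE rates:

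| SAE rates | True deaths | Deaths seen |
|---|---|---|
| 5% vs 10% | 3.4% vs 4.8% | 1.9% vs 1.8% |
| 5% vs 20% | 3.4% vs 7.6% | 1.9% vs 1.6% |
| 5% vs 30% | 3.4% vs 10.4% | 1.9% vs 1.4% |
| 10% vs 20% | 4.8% vs 7.6% | 1.8% vs 1.6% |

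These are the extreme case. If a share *c* of deaths after an SAE is still captured, the difference seen at 5% vs 20% is (1.6 + 6.0*c*) − (1.9 + 1.5*c*) = −0.3 + 4.5*c* points. With *c* = 0 it is −0.3, with *c* = 0.5 it is +1.95, and with *c* = 1 it is the true +4.2. The ranking reverses only if *c* is below 0.3/4.5, about 7%. Above that the difference is diluted, not reversed.

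**Direction for recovery**

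Assume 28-day recovery of 85% without an SAE and 40% after one, with SAE rates again 5% vs 20%.

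| Handling of withdrawn patients | 5% arm | 20% arm | Difference (points) |
|---|---|---|---|
| Followed to day 28 | 0.95 × 85 + 0.05 × 40 = 82.75% | 0.80 × 85 + 0.20 × 40 = 76.0% | −6.75 |
| Excluded | 85% | 85% | 0 |
| Counted as not recovered | 0.95 × 85 = 80.75% | 0.80 × 85 = 68.0% | −12.75 |

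Exclusion hides the deficit and counting as not recovered enlarges it.

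A simulation of time to recovery agrees (100 patients per arm, 1000 runs; mean recovery time 8 days, slowed to 50 days after an SAE on days 1 to 7). The approximate recovery hazard ratio was 0.84 with full follow-up, 0.99 with censoring at the SAE, and 0.78 with withdrawn patients counted as not recovered.

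**The unnamed end point**

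Clinical recovery requires sustained normalisation, so a progressing patient cannot meet it. Respiratory progression is a separate secondary endpoint. Neither the flow diagram nor the re-randomisation text says which endpoint has been reached.

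**The case against.** The strongest reply is that the protocol does distinguish stopping treatment from leaving the trial. The discontinuation section speaks of treatment throughout, and the SAE sentence, placed under Dose Modifications, may be loosely worded. This stands in part: the defect is one sentence at odds with the rest, not a design without the distinction. But that sentence is the specific and mandatory rule for SAEs, so staff following the text would apply it.

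Second, the Adverse Event Log has codes for a fatal outcome and for grade 5, so a death from the SAE itself can be recorded. This also stands, and is why the 1.9% vs 1.6% figure is an extreme. The log does not cover a later, unrelated death, subsequent ventilation, recovery or viral clearance. The outcome lists on the follow-up forms carry no vital-status or day-28 item. The proportion of patients with at least one SAE is not affected.

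Three stronger readings are tempting, and the documents do not support them.

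- **Progression is scored as recovery.** No text says so, the definition of clinical recovery rules it out, and the case report form records recovery separately. The label is undefined, not miscoded.
- **Progressing patients leave follow-up.** They are moved to institute treatment; nothing says that observation ends.
- **The rule favours the more toxic arm.** That holds if withdrawn patients are excluded or censored and reverses if they count as not recovered. Because the rule covers SAEs of any cause, the arm with more exits could be standard treatment.

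Nor are two neighbouring details errors. The two statements of observation length agree if 28 days is the minimum. The 72-hour check asks about improvement, and recovery can be confirmed later.

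**Conclusion.** The contradiction is real and should be corrected in the protocol itself. The SAE sentence cannot be reconciled with 28-day follow-up, an analysis of all randomised patients, the mortality and ventilation endpoints, or the treatment-only discontinuation wording. Applied as written, it causes informative loss of outcomes after a first SAE.

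The size cannot be derived from the protocol. On the assumed rates, a true mortality difference of 4.2 points shrinks towards nothing as fewer post-SAE deaths are captured, and is slightly reversed if almost none are. The direction of bias in recovery cannot be stated in advance, because the handling of withdrawn patients is not given and the arm with more SAEs is not known.

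The unnamed end point is a definitional gap. It leaves room for inconsistent coding but does not itself turn failure into recovery.

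**What to change.** 1. Reconcile the SAE sentence with the discontinuation section. When study drug stops is a clinical decision for the investigators, and this point proposes no rule for it.
2. State that stopping study drug, for an SAE or any other reason, does not end follow-up. Every randomised patient who has not withdrawn consent to data collection is followed to day 28 and analysed in the randomised arm.
3. Replace the two unnamed end-point phrases, in the flow diagram and in the re-randomisation text, with a named treatment-failure or progression event. State that this event is not clinical recovery and that a patient who dies counts as not recovered.

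The cost is protocol wording, plus a day-28 status check by telephone or from records for patients who stop study drug. That check lies within the 28-day follow-up already planned.

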**D. Study related Information:**

| 1. **Design of study:** Epidemiological ⬜ Basic Sciences ⬜ Behavioral ⬜   Clinical ⬜ Interventional � ✔ Single Centre ⬜ Multicentre ⬜ |
| --- |
| 1. **No. of participants: AIIMS, Rishikesh Total (if multicentre)**   **Patient total = all patients who presented within the study period**  **Control**   1. **Duration of study: 6 months** 2. **Duration of subject participation (no. of visit by a participant in study): 28 days OR till patient is discharged or death whichever is longer ✔** |

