**Country ____________State___________________District_____________________Lane_________________**

**CLINICAL INCLUSION CRITERIA**

| One or more of these during this illness | A history of self-reported feverishness or documented fever | ☐Yes ☐No |
| --- | --- | --- |
|  | Cough | ☐Yes ☐No |
|  | Dyspnoea (shortness of breath) OR Tachypnoea | ☐Yes ☐No |
|  | Clinical suspicion of ARI despite not meeting criteria above | ☐Yes ☐No |

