**CLINICAL FEATURES (Unk = Unknown)**

| - Cough and sputum production - Sore throat - Chest pain - Shortness of breath - Confusion | ☐Yes ☐No ☐Unk  ☐Yes ☐No ☐Unk  ☐Yes ☐No ☐Unk  ☐Yes ☐No ☐Unk  ☐Yes ☐No ☐Unk | - Seizures - Vomiting - Nausea - Diarrhoea - Conjunctivitis - Myalgia - Other, specify_______ | ☐Yes ☐No ☐Unk  ☐Yes ☐No ☐Unk  ☐Yes ☐No ☐Unk  ☐Yes ☐No ☐Unk  ☐Yes ☐No ☐Unk  ☐Yes ☐No ☐Unk  ☐Yes ☐No ☐Unk |
| --- | --- | --- | --- |

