**LABORATORY RESULTS ON FOLLOW UP (*record units if different from those listed)**

| Parameter | Value | Not done | Parameter | Value | Not done |
| --- | --- | --- | --- | --- | --- |
| Haemoglobin (g/L) |  |  | Urine R/M (significant if any) |  |  |
| WBC count (x109/L |  |  | Sodium (mEq/L |  |  |
| Haematocrit (%) |  |  | Potassium (mEq/L) |  |  |
| Platelets (x109/L) |  |  | Calcium(mg/dL) |  |  |
| APTT/PT/INR |  |  | Lactate (mg/dL) |  |  |
| Total bilirubin (mg/dL) |  |  | Procalcitonin (ng/mL) |  |  |
| Direct bilirubin (mg/dL) |  |  | CRP (mg/L) |  |  |
| Albumin (g/dl) |  |  | LDH (U/L) |  |  |
| Globulin (g/dl) |  |  | Creatine kinase (U/L) |  |  |
| SGOT/SGPT (U/L) |  |  | Troponin (ng/mL) |  |  |
| Urea (mg/dL) |  |  | ESR (mm/hr) |  |  |
| Creatinine (mg/dL) |  |  | D-dimer (mg/L) |  |  |
| Others |  |  |  |  |  |

Influenza virus: ☐Positive ☐Negative ☐Not done If positive, type ______________

Coronavirus: ☐ Positive ☐Negative ☐ Not done If positive: ☐ MERS-CoV ☐SARS-CoV-2 ☐Other

Other respiratory pathogen: ☐Positive ☐ Negative ☐Not done If positive, specify:___________

Other pathogen of public health interest detected: If yes, specify: __________________________

Radiological Investigations (if performed):

1. Chest X Ray/CT Performed (report):
2. Ultrasonography:
3. Others

Previous Treatment Regime (If any-to specify group with duaration):

☐Non-Severe Treatment arms (NS-group): Treatment Arm-A: ___________________________

Outcomes:

1. Clinical recovery ☐Yes ☐No
2. Time to 2019-nCoV RT-PCR negative in upper respiratory tract specimen in days (if applicable):
3. Time to defervescence in hours (if applicable)
4. Serious adverse events (specify if any)
5. **Final Clinician’s Impression:**

1. [↑](#footnote-ref-1)
2. **Severe Treatment arms (S-group)**

   **PARTICIPANT ID** I___I I___I I___I I___I I___I -- I___I I___I I___I I___I **Date of enrolment** [__][__]/[__][__]/[__][__][__][__]

   **Day of Hospitalization: _______________ Date of follow-up:** [__][__]/[__][__]/[__][__][__][__]

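### Time to clinical recovery needs a four-level patient-reported cough grade, but the follow-up forms record only a combined cough-and-sputum Yes/No/Unknown tick, so the cough component cannot be derived or checked for patients ticked Yes or Unknown

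*Protocol*

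**What the plan says.** **Definition.** The protocol, item (e), Endpoints, lists TTCR first among the primary endpoints. It runs in hours from the start of study treatment "until normalisation of fever, respiratory rate, and oxygen saturation, and alleviation of cough, sustained for at least 72 hours". The cough criterion is "Cough- mild or absent on a patient reported scale of severe, moderate, mild, absent", so the deciding cut lies between mild and moderate, and the patient supplies the grade.

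**Forms.** The case report form is part of the same document.

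- Enrolment, Clinical Inclusion Criteria: under "One or more of these during this illness", cough is a Yes/No box. It stands alone, apart from sputum.
- Non-severe follow-up form, Clinical Features: "Cough and sputum production", with Yes, No and Unk boxes.
- Severe follow-up form, Clinical Features: the same combined item and boxes.
- Both follow-up forms, Outcomes: "Clinical recovery ☐Yes ☐No". The same blocks ask for a duration in days for RT-PCR negativity and in hours for defervescence.
- Both follow-up forms have fields for temperature, respiratory rate and oxygen saturation (with room-air or oxygen status), and each is headed with a date of follow-up.

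**The concern.** Three of the four TTCR components can be read from the forms. The fourth, cough, is defined at a cut-point that the forms do not record. If the forms are used as written, there are two ways to fill the gap.

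1. Treat a Yes as not recovered. The endpoint then becomes absence of cough, which is stricter than the definition, and nobody will have decided to change it.
2. Rely on the clinical recovery tick. The first primary endpoint then rests on a judgement, in an open-label trial, whose cough part cannot be checked against recorded data.

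This gap is not something to leave to a statistical analysis plan. Such a plan can specify how to derive an endpoint, but it cannot restore a severity grade that was never collected. Once a follow-up visit has passed, the patient's own rating on that day is lost.

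**Working it through.** The contradiction is not numerical, so the first step sets the definition against the form. The second step illustrates the size of the shift. The protocol states no figure of its own to reproduce.

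**Step 1. Form entry against TTCR cough criterion**

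| Form entry | Levels on the protocol's scale | Criterion met? |
| --- | --- | --- |
| No | absent | yes |
| Yes | mild, moderate or severe | mild yes; moderate and severe no; cannot be told apart |
| Unk | any | missing |

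The combined label adds a smaller ambiguity: it does not say how to tick a cough without sputum.

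**Step 2. Timing.** TTCR is in hours with a 72-hour persistence rule. The recovery tick can be dated only by the follow-up date of the form it sits on. There is no hour and no field for when recovery began.

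**Step 3. Illustration of reading Yes as unrecovered.** The protocol gives no cough durations, so every input here is an assumption:

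- every patient starts with moderate or severe cough;
- times are independent and exponential;
- median time to mild-or-absent cough is *m* = 4 or 5 days;
- median time for the other signs to normalise is 4 days;
- the further median time from mild to absent cough is *r* = 2 to 8 days.

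Under the protocol's rule, the share meeting all criteria by day *t* is

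F(t) = (1 − 2^(−t/m)) × (1 − 2^(−t/4)).

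- *m* = 4: setting F = 0.5 gives 1 − 2^(−t/4) = √0.5 = 0.707, so t = 7.1 days.
- *m* = 5: F = 0.5 at t = 8.0 days.

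If Yes means unrecovered, the first factor is replaced by the distribution of the sum of two exponential times. With a = ln 2/m and b = ln 2/r,

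G(t) = 1 − [b·e^(−at) − a·e^(−bt)]/(b − a).

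- *m* = 4, *r* = 2: here b = 2a, so G(t) = (1 − 2^(−t/4))², and the full product is (1 − 2^(−t/4))³. Setting this to 0.5 gives 1 − 2^(−t/4) = 0.794, so t = 9.1 days.
- *m* = 5, *r* = 8: at t = 16.5 days, G = 0.530 and the other factor is 0.943; the product is 0.50.

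The medians move from 7.1–8.0 days to 9.1–16.5 days across these inputs. Day 25 is the last day on which the criteria can first be met and still hold for 72 hours within a 28-day window (28 − 3 = 25). The share that has not met them by then is 1 − F(25):

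| Rule | Lowest | Highest |
| --- | --- | --- |
| Protocol | 2.6% (*m* = 4) | 4.4% (*m* = 5) |
| Yes = unrecovered | 3.9% (*m* = 4, *r* = 2) | 26% (*m* = 5, *r* = 8) |

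**Step 4. Power.** The effect on power has no fixed sign. If a drug speeds recovery to mild cough but leaves residual mild cough unchanged, the stricter rule dilutes the contrast. If it shortens the residual phase in the same proportion, the stricter rule can add power. The protocol gives no basis for choosing. It also has no planned size ("Patient total = all patients who presented within the study period") and no stated effect, so no power figure is given here.

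**The case against.** **Part of the endpoint survives.** The other three components are recorded, and a patient ticked No for cough meets the criterion on the natural reading. A reader might infer that TTCR cannot be scored for anyone. The forms do not support that: the failure is confined to entries of Yes or Unk.

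**Some timing exists.** A reader might infer that recovery is undated. Each follow-up form carries a date, so if the form is completed at every assessment, the first Yes for clinical recovery can be dated to that day. What is missing is the hour and an explicit recovery time.

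**An evaluator could apply the scale at the bedside.** The protocol assigns clinical evaluations to a separate investigator, who could ask the four-level question and tick recovery accordingly. This is fair, but it is not blinding, the protocol does not direct that the answer be written down, and the tick still could not be audited.

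**A patient with severe dry cough ticked No.** The combined label makes this possible, but no form instruction leads to it. It is an ambiguity and not an expected error.

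**The illustration shows only that a stricter rule is met later.** This stands. The size rests on assumed durations, and the contradiction does not depend on it.

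**Weight.** This is one component of one of three listed primary endpoints in a trial that calls itself exploratory. That limits the consequences, but it does not excuse a named primary endpoint that its own forms cannot support.

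**Conclusion.** The protocol's definition and its forms contradict each other on cough. For any patient ticked Yes or Unk at follow-up, the cough component of TTCR cannot be derived or verified from the form. Treating Yes as unrecovered replaces the stated criterion with absence of cough and delays recovery for everyone who passes through a mild-cough phase. Under the illustrative assumptions, the median moves from about 7–8 days to about 9–16.5 days. The true delay is unknown because the protocol gives no cough durations.

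A reader might also infer that the mismatch must cost power. The documents do not support this, since the direction depends on whether treatment shortens residual mild cough. The conclusion rests only on the text of the definition and the fields on the forms, and needs none of the assumed figures.

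**What to change.** 1. On both follow-up forms, replace the combined item with a patient-reported cough grade (absent, mild, moderate, severe) and a separate sputum Yes/No.
2. Grade the existing enrolment cough item on the same four levels. It is already separate from sputum.
3. Beside the clinical recovery tick, add the date and time at which all four criteria were first met.
4. Derive TTCR, including the 72-hour persistence, from the recorded components. The staff tick then serves as a cross-check.

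If the investigators prefer the item as it stands, the alternative is to reword the cough criterion to match it, by a deliberate amendment.

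The cost is one form revision with a few extra boxes. It needs no additional visit, test or patient. It should be done before follow-up data are collected, because the grade cannot be reconstructed from the forms afterwards.
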